### Sample processing

The aspirates are sent directly to the hospital's pathology laboratory for pepsin detection or, if outside pathology opening hours, stored at 4°C until the laboratory opens. Tamworth and Port Macquarie hospitals have access to a 24 hour pathology laboratory, while Coffs Harbour hospital's pathology service operates between 0700-2400 hours. Each laboratory is blinded to the conduct of CP during the intubation.

### Sample size

In order to adequately power the trial the variation in the rates of aspiration reported in the literature (0.8% to 22%) must be reconciled. Sellick's original data indicates a rate of 11% [2]. Therefore, assuming a rate of 11% aspiration in the control arm, 0% aspiration in the intervention arm and a power of 90% (alpha error = 0.05), 106 patients must be randomised to each group.

### Analysis

Continuous measurements will be expressed with means and standard deviations. Frequencies will be published the variables of interest. Two group comparisons will be undertaken using the Chi-squared test or Fisher's exact test where appropriate. Comparisons of means will utilise an independent *t *test. Ordinal and continuous variables will be compared using a Mann-Whitney test.

### Staff education

All staff assisting with the trial will complete a mandatory education DVD to ensure uniformity can be maintained across the participating hospitals. The DVD consists of an explanation of the trial, reviewing the anatomy of the upper airway, standardising location of the cricoid ring, delivery of 30 - 40 N CP during the intubation, operation of the scales and serial data recorder, and data collection.

## Discussion

The primary aim of this study is two-fold. Firstly, by comparing the incidence of aspiration of pepsin in the intervention and control groups and prospectively documenting the benefits and adverse events associated with 30 - 40 N of cricoid force during RSI, it aims to challenge the notion that CP prevents aspiration. Secondly, since the presence of pepsin in the oropharynx will be indicative of aspiration having occurred prior to intubation by virtue of the injury sustained by the patient, determining the incidence of pre-intubation aspiration will allow us to further evaluate the relevance of CP in the RSI algorithm in ED.

The secondary aim of this study is also two-fold. Firstly, defining any observed correlation between aspiration and pre-intubation Glasgow coma score will provide evidence for indications for the use of CP dependent upon the level of patient consciousness. Secondly, a correlation between detection of pepsin in trachea and development of aspiration syndromes will support the use of Fibrinogen plate assay in a clinical setting for their early detection and treatment.

It is conceivable that this research could also give rise to novel therapy. For example, once the incidence of serious aspiration and a pepsin positive assay is identified, the plate assay for pepsin could potentially be performed at the bedside, enabling doctors to treat aspiration pneumonia much earlier. It may also lead to amendments to the algorithm for RSI if CP is found to be deleterious.

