**Discussion:**

The benefits and risks of cricoid pressure application will be scrutinised by comparison of the incidence of aspiration and difficult or failed intubations in each group. The role of cricoid pressure in RSI in the emergency department and the use of a pepsin detection as a predictor of clinical aspiration will be evaluated.

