### Study design

This is a prospective randomised blinded controlled study of RSI and CP application within the ED. Due to ethical considerations, a control group without CP applied cannot be included in any study. Instead, this study will exploit the fact that the target range CP of 30 - 40 newtons (N) was applied only 25% of the time by ED staff when tested on a model larynx [29]. The incidence of aspiration (determined by pepsin detection in the trachea) in two groups of patients will be compared; those with conventional CP (and hence about a 25% chance of target range CP), and those with exact sustained target range CP (using weighing scales for direct biofeedback). Longitudinal follow-up of participants will be performed to determine to what degree detection of pepsin in the trachea correlates with the development of clinical aspiration syndromes. In addition the incidence of aspiration as a result of pre-hospital intubation (determined by pepsin detection in the trachea) will be determined.

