#### Secondary aims

• Determine whether a relationship exists between the incidence of aspiration and pre-intubation Glasgow coma score (GCS).

• Determine any correlation between pepsin detection in aspirates and development of clinical aspiration syndromes.

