#### Pepsin assay

Ufberg's pepsin plate assay is reliant upon test samples containing enzymatically active pepsin. Pepsin activity is highly sensitive to pH with maximum activity between pH 1.5-2.5 and irreversible inactivation occurring above pH 7.5 [43]. Pepsin stored in gastric juice samples at 4°C remains active for up to 3 days (evaluated up to pH 6)[44]. The pH of saliva sampled from patients following episodes of gastric regurgitation has been reported to range from 7-8 [45]. Therefore citric acid (pH 2.5) will be added to aspirates to ensure pepsin activity is maintained prior to testing.

The laboratory will perform the qualitative pepsin plate assay based on fibrinogen digestion according to the method of Ufberg *et al*. [39]. Briefly, 1.25% agarose plates are prepared with bovine fibrinogen (in normal saline) added to a final concentration of 1 mg/ml. Four wells are punched into the agarose, each capable of holding 7 μl of test sample. Porcine pepsin (positive control) and normal saline (negative control) are included on each plate along with a sample of each aspirate from one patient. The plates are left in a humid chamber for up to 24 hours when they are read by visual inspection. A positive result is recorded if there is visible clearing zone around a well. No clearing zone visible after 24 hours is recorded as a negative result. The plate is checked progressively after sample addition initially every 2 hours, in this way a positive tracheal result can be communicated to the clinician.

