### Data collection

After the intubation is complete the personnel involved complete a data sheet included in the trial enrollment pack. Data recorded includes patient demographics, procedural details, procedural and post-intubation complications encountered.

*Patient demographic details*; age, date & time of intubation and medical record number (for 28 day follow-up).

*Procedural details*; location of intubation (ED or pre-hospital), lowest pre-intubation GCS, intubation drugs used, experience of intubation operator, evidence and nature of macroscopic aspirate seen and grade of laryngoscopic view obtained.

*Procedural complications*; 3 or more attempts to place the ETT in the trachea, > 10 minutes using conventional laryngoscopy, required change of operator, termination of the attempt at RSI, use of laryngeal mask or surgical airway.

*Post-intubation complications encountered within 30 minutes of RSI*; severe hypotension (Systolic blood pressure < 60 mmHg), severe hypoxaemia (SaO_2 _< 70%), death and cardiac arrest.

The data sheet and SD card containing weight data will be sent to the Trial Coordinator who will enter the data into a password-protected database. Each episode of RSI has a unique randomly assigned number within the database (Plate Number). This number will be linked to the episode of service, and the pepsin assay result will be automatically appended to the corresponding patient data set in the database. The investigators are therefore blinded to the results coming in from the laboratory.

At 28 days the patient notes will be reviewed. The acute physiology and chronic health evaluation (APACHE II) score and diagnostic code will be determined and any treatment for aspiration as an inpatient (discharge diagnosis of aspiration pneumonitis/pneumonia or antibiotic therapy explicitly instituted to treat for aspiration pneumonia) will be noted.

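### A correlation between tracheal pepsin and aspiration syndromes would not by itself support clinical use of the plate assay; that inference needs accuracy estimates

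*Protocol article*

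**What the plan says.** The relevant statements in the protocol article are these.

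- **Secondary aims:** "Determine any correlation between pepsin detection in aspirates and development of clinical aspiration syndromes".
- **Study design:** follow-up is meant "to determine to what degree detection of pepsin in the trachea correlates with the development of clinical aspiration syndromes".
- **Abstract, Discussion paragraph:** "the use of a pepsin detection as a predictor of clinical aspiration will be evaluated".
- **Discussion:** "a correlation between detection of pepsin in trachea and development of aspiration syndromes will support the use of Fibrinogen plate assay", and the sentence ends "in a clinical setting for their early detection and treatment".
- **Pepsin assay:** the result is binary: "A positive result is recorded if there is visible clearing zone around a well"; otherwise it is negative.
- **Data collection:** the clinical outcome at the 28-day note review is also binary: "discharge diagnosis of aspiration pneumonitis/pneumonia or antibiotic therapy explicitly instituted to treat for aspiration pneumonia".
- **Analysis:** for categorical data, "Two group comparisons will be undertaken using the Chi-squared test or Fisher's exact test where appropriate". No correlation coefficient is named.

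The Background describes the assay as validated, sensitive and specific, but as a marker of aspiration. It adds that the cited assay study had no longitudinal follow-up linking pepsin to later syndromes. Accuracy for syndromes is therefore the open question here.

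**The concern.** The Abstract asks whether pepsin predicts clinical aspiration. The Secondary aims and Study design ask about correlation. The Discussion then moves from a correlation to support for using the test on patients. Those are different questions. In a 2x2 table, a non-zero association means only that the syndrome rate differs between pepsin-positive and pepsin-negative patients. A test meant for early detection is judged by the share of syndromes it picks up and the share of its positives that are true, and both can be poor while the association is clear.

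What is at stake is the wording of a conclusion. A modest association could be reported as favouring clinical use of the assay when the same table shows that most positives are false.

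**Working it through.** **The plan's own figure.** The only figure it derives is the sample size: 11% versus 0%, 90% power, alpha 0.05, 106 per group. With mean proportion 0.055, two-sided:

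n = [1.96 × √(2 × 0.055 × 0.945) + 1.2816 × √(0.11 × 0.89)]² / 0.11² = (0.632 + 0.401)² / 0.0121 ≈ 88.2, so 89.

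The continuity correction gives (88.2/4) × [1 + √(1 + 4/(88.2 × 0.11))]² ≈ 105.6, so 106. The stated figure reproduces and is not at issue.

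**Inputs for the illustration.**
- N = 212 (Abstract, Methods/design).
- Pepsin-positive rate q = 0.22 (Background, emergency department intubations in the cited assay study).
- Syndrome rate p: not given in the documents; assumed 5%, 10%, 15% and 20%.
- Strength of association: not given; assumed phi = 0.2.

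**Formulas.**
- Chi-squared (1 df) = N × phi² = 212 × 0.04 = 8.48, p = 0.0036.
- P(both) = p × q + phi × √[p(1 − p) q(1 − q)]
- Sensitivity = P(both)/p; specificity = 1 − (q − P(both))/(1 − p)
- PPV = P(both)/q; NPV = 1 − (p − P(both))/(1 − q)

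**Worked case, p = 0.15.**
- √(0.15 × 0.85 × 0.22 × 0.78) = 0.1479, so P(both) = 0.0330 + 0.2 × 0.1479 = 0.0626.
- Sensitivity = 0.0626/0.15 = 42%. On 0.15 × 212 ≈ 32 cases, the Wilson 95% CI is about 26% to 59%.
- Specificity = 1 − 0.1574/0.85 = 81%.
- PPV = 0.0626/0.22 = 28%.
- NPV = 1 − 0.0874/0.78 = 89%.

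**Across the assumed syndrome rates, phi = 0.2 throughout.**

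| Syndrome rate | Sensitivity | Specificity | PPV | NPV |
|---|---|---|---|---|
| 5% | 58% | 80% | 13% | 97% |
| 10% | 47% | 81% | 21% | 93% |
| 15% | 42% | 81% | 28% | 89% |
| 20% | 39% | 82% | 35% | 84% |

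With a stronger assumed association, phi = 0.3 at a 15% rate, chi-squared is 212 × 0.09 = 19.08 (p about 0.00001) and PPV is still 35%.

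**Check with whole patients.** Take 47 positives (22%) and 21 syndromes (an assumed 10%). The weakest positive association with two-sided Fisher p < 0.05 is 9 true positives, 38 false positives, 12 false negatives and 153 true negatives: p = 0.025, phi = 0.17. Sensitivity is 9/21 = 43% (95% CI 24% to 63%), PPV 9/47 = 19% (10% to 33%), specificity 153/191 = 80% and NPV 153/165 = 93%. So 12 of 21 syndromes are missed and 38 of 47 positives are false.

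Repeating this for positive rates of 5.5%, 11% and 22% and assumed syndrome rates of 5%, 10% and 20%, the weakest such tables have phi 0.16 to 0.22, sensitivity 14% to 55% and PPV 13% to 50%. The p < 0.05 cut-off is used here only to define a detectable correlation; the article sets none for this aim.

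**The case against.** The strongest reply is that the article commits to very little. The sentence stands in the Discussion, not under Analysis or Outcome measures. It says the correlation will lend support, not that it will establish anything, and the next paragraph speaks of bedside use only as a possibility. Study design asks about the degree of correlation, which is a question of size, and the Abstract already states the predictive aim. The word correlation may simply be loose for relationship. The choice of accuracy measures for a secondary aim is also commonly left to a full protocol or analysis plan, neither of which is shown.

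Much of this stands. A reader might infer that the article fixes a decision rule, that a significant correlation would lead the trial to endorse bedside use, or that accuracy measures have been left out of the plan. The documents support none of these: they name no significance criterion, coefficient or adoption threshold, and silence in a condensed article is not an omission.

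The illustration has limits too. The syndrome rates and phi are assumptions, and 22% is a single literature figure. Sensitivity is above one half at a 5% syndrome rate, so it cannot be said that the assay would miss most cases throughout. NPV of 84% to 97% belongs in any fair account, although always predicting no syndrome would be right in 80% to 95% of patients at the same rates.

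What does not fall is the inference itself. The article names the evidence, a correlation, and the conclusion it would support, clinical use for early detection and treatment. Accuracy measures in an unseen plan would not make that sentence correct.

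**Conclusion.** The point holds as a correction to a stated inference on a secondary aim. Presence of a correlation between tracheal pepsin and aspiration syndromes is not evidence of predictive accuracy, and the Discussion should not rest support for clinical use on it. Under the assumptions above, an association with p about 0.004 is compatible with 65% to 87% of positives being false (PPV 35% down to 13%) and 42% to 61% of syndromes being missed (sensitivity 58% down to 39%). These figures show what is possible at this sample size; they do not forecast the trial's result. That association differs from accuracy needs no assumption.

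**What to change.** - For this secondary aim, report sensitivity, specificity, PPV, NPV and likelihood ratios of tracheal pepsin for the 28-day aspiration outcome, each with a 95% confidence interval. State the aim as evaluating pepsin as a predictor, in line with the Abstract.
- Reword the Discussion sentence so that any support for clinical use rests on those estimates, not on the presence of a correlation.

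The cost is a change of wording and a few lines of analysis. The measures come from the same 2x2 table, with no new patients, samples or follow-up.

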## Trial status

Ongoing.

## List of abbreviations

ANSWER: Amalgamated New South Wales Emergency Research; ANZCTR: Australian New Zealand Clinical Trials Registry; APACHE: Acute Physiology and Chronic Health Evaluation; CP: cricoid pressure; CPR: cardiopulmonary resuscitation; DVD: Digital Versatile Disc; ED: Emergency Department; ETT: Endotracheal Tube; GCS: Glasgow Coma Score; N: newton; NSW: New South Wales; RSI: Rapid Sequence Intubation; SD: Secure Digital.

